**LIST OF ABBREVIATIONS AND RELEVANT DEFINITIONS**

|                |                                                                                                                                                                                                                                                                                                                                                  |
|----------------|--------------------------------------------------------------------------------------------------------------------------------------------------------------------------------------------------------------------------------------------------------------------------------------------------------------------------------------------------|
| ABR     | ABR form, General Assessment and Registration form, is the application form that is required for submission to the accredited Ethics Committee (In Dutch, ABR = Algemene Beoordeling en Registratie)                                                                                                                                      |
| AE      | Adverse Event                                                                                                                                                                                                                                                                                                                             |
| AR      | Adverse Reaction                                                                                                                                                                                                                                                                                                                          |
| CA      | Competent Authority                                                                                                                                                                                                                                                                                                                       |
| CCMO    | Central Committee on Research Involving Human Subjects; in Dutch: Centrale Commissie Mensgebonden Onderzoek                                                                                                                                                                                                                               |
| CV      | Curriculum Vitae                                                                                                                                                                                                                                                                                                                          |
| DSMB    | Data Safety Monitoring Board                                                                                                                                                                                                                                                                                                              |
| EU      | European Union                                                                                                                                                                                                                                                                                                                            |
| EudraCT | European drug regulatory affairs Clinical Trials                                                                                                                                                                                                                                                                                          |
| GCP     | Good Clinical Practice                                                                                                                                                                                                                                                                                                                    |
| IB      | Investigator's Brochure                                                                                                                                                                                                                                                                                                                   |
| IC      | Informed Consent                                                                                                                                                                                                                                                                                                                          |
| IMP     | Investigational Medicinal Product                                                                                                                                                                                                                                                                                                         |
| IMPD    | Investigational Medicinal Product Dossier                                                                                                                                                                                                                                                                                                 |
| METC    | Medical research ethics committee (MREC); in Dutch: medisch ethische toetsing commissie (METC)                                                                                                                                                                                                                                            |
| (S)AE   | (Serious) Adverse Event                                                                                                                                                                                                                                                                                                                   |
| SPC     | Summary of Product Characteristics (in Dutch: officiële productinformatie IB1-tekst)                                                                                                                                                                                                                                                      |
| Sponsor | The sponsor is the party that commissions the organisation or performance of the research, for example a pharmaceutical company, academic hospital, scientific organisation or investigator. A party that provides funding for a study but does not commission it is not regarded as the sponsor, but referred to as a subsidising party. |
| SUSAR   | Suspected Unexpected Serious Adverse Reaction                                                                                                                                                                                                                                                                                             |
| Wbp     | Personal Data Protection Act (in Dutch: Wet Bescherming Persoonsgegevens)                                                                                                                                                                                                                                                                 |
| WMO     | Medical Research Involving Human Subjects Act (in Dutch: Wet Medisch-wetenschappelijk Onderzoek met Mensen)                                                                                                                                                                                                                               |

## SUMMARY

**Rationale:** In acute myocardial infarction early restoration of coronary blood flow is the most effective strategy to limit infarct-size. Paradoxically, reperfusion itself also aggravates myocardial injury and contributes to final infarct size, a process termed 'reperfusion injury'. Ischemia and reperfusion (IR)-induced endothelial dysfunction seems to play a pivotal role in this process, resulting in vasoconstriction and reduced blood flow to the already ischemic tissue. Recently, it has been shown that the glucose-lowering drug metformin is able to limit IR-injury in murine models of myocardial infarction, probably by increased formation of the endogenous nucleoside adenosine. In the current research proposal, we aim to translate this finding to the human in vivo situation, using flow-mediated dilation (FMD) of the brachial artery as a well-validated model of (endothelial) IR-injury.

**Objective:** To study the protective effect of pre-treatment with metformin on flow mediated dilation after 20 minutes ischemia and 20 minutes reperfusion. If metformin treatment indeed limits endothelial IR-injury, a second, unblinded study will be performed in the same subjects to investigate whether this is mediated by adenosine receptor stimulation.

**Study design:** Randomized, single blind, , cross over clinical trial.

**Study population:** Healthy volunteers (n= 26 for both studies), age 30-50 years.

**Intervention:** *Main study (metformin FMD trial):* Pre-treatment with metformin 500 mg three times a day for 3 days or no medication. *Second study:* Pre-treatment with metformin 500 mg three times a day for 3 days or no medication, combined with caffeine infusion preceding FMD measurement.

**Main study parameters/endpoints:** Difference in flow mediated dilation before and after 20 minutes of ischemia.

**Nature and extent of the burden and risks associated with participation, benefit and group relatedness:** Healthy volunteers will be treated with metformin (500mg three times a day) for 3 days. Short-term treatment with metformin is not expected to induce serious side-effects. Monotherapy with metformin does not induce hypoglycemia. Metformin can give some gastrointestinal discomfort in the first days of treatment, but this is mild and self-limiting. Lactic acidosis is a rare, but serious, complication of metformin, which can occur in the setting of shock/hypoxia/renal failure in combination with metformin accumulation. This is therefore not to be expected in case of healthy volunteers. The participants will not benefit directly from participating in this study, but if our hypothesis proves to be correct, these findings will help to optimize future medical care of patients suffering from (myocardial) ischemia/infarction.

## 1. INTRODUCTION AND RATIONALE

In patients with an acute myocardial infarction early restoration of coronary blood flow is the most effective strategy to limit infarct-size. Paradoxically, reperfusion itself also aggravates myocardial injury and contributes to final infarct-size, a phenomenon that has been termed 'reperfusion injury'. Ischemia and reperfusion (IR)-induced endothelial dysfunction seems to play a pivotal role in this process, where impairment in endothelium-dependent vasodilatation and an exaggerated response to endothelium-dependent vasoconstrictors result in vasoconstriction and reduced blood flow to ischemic areas. Based on the high residual morbidity and mortality in patients suffering a myocardial infarction, novel strategies to reduce this injury are urgently needed.

In an effort to limit IR injury, a number of mechanisms that may display cardioprotective properties have been identified. An important mechanism involves activation of adenosine monophosphate-activated protein kinase (AMPK). Immediately after the onset of myocardial ischemia, AMPK is activated by phosphorylation, and remains activated for more than 24 hours following reperfusion. The antihyperglycemic drug metformin has been suggested to activate AMPK and has recently been found to exhibit cardioprotective properties in murine models of myocardial infarction. Metformin activates AMPK by increasing the intracellular AMP concentration, probably by inhibiting complex 1 of the mitochondrial respiratory chain. We hypothesized that the increase in intracellular AMP also facilitates the formation of the endogenous purine adenosine. Since adenosine receptor stimulation is known to increase tolerance against IR, this mechanism may well contribute to the cardioprotective effect of metformin. Indeed, the cardioprotective effect of metformin appeared to be completely abolished by a nonselective adenosine receptor antagonist in a rat infarction model.

In the current study, we aim to translate the promising prospects of metformin to the human in vivo situation. First, we want to conduct an experiment in which healthy volunteers will be treated with or without metformin prior to an IR event to study whether metformin can also limit IR-injury in humans in vivo. As a model for IR-injury of the endothelium, we will use flow-mediated dilatation (FMD) of the brachial artery after a period of forearm ischemia and reperfusion. If proven effective, a second experiment will be conducted in which the adenosine receptor antagonist caffeine is co-administered with metformin to study whether the protective effect is indeed mediated by adenosine receptor stimulation. Flow mediated dilation represents a largely NO-mediated endothelium-dependent dilation and has been shown to be decreased after forearm

ischemia and reperfusion, indicating IR-injury of the endothelial lining. Previous studies have validated FMD as a model for endothelial IR-injury, and showed that this reduction in FMD after ischemia and reperfusion can be prevented by several interventions that are known to prevent ischemia reperfusion injury (e.g. ischemic preconditioning, remote preconditioning, ischemic postconditioning, bradykinin administration, NO administration and statins). FMD of the brachial artery as a measure of endothelial (dys)function is therefore a well validated model to study effects of possible protective strategies and perform mechanistic experiments on IR-injury in humans in vivo.

## 2. OBJECTIVES

### Primary Objective:

#### *Metformin-FMD trial:*

To study the effect of oral pretreatment with metformin (500 mg three times a day for 3 days) on flow mediated dilation of the brachial artery after 20 minutes of forearm ischemia and 20 minutes reperfusion in healthy volunteers.

#### *Control study:*

To study whether caffeine, a non-selective competitive antagonist of adenosine receptors, attenuates the protective effect of metformin on flow mediated dilation after 20 minutes ischemia and 20 minutes reperfusion in healthy volunteers.

**Secondary Objective(s):** not applicable.

### 3. STUDY DESIGN

After written informed consent all healthy volunteers will undergo medical screening consisting of a short interview, physical examination, laboratory evaluation (glucose, cholesterol, kreatinine) and EKG. Females using oral contraceptives will be asked to continue their contraceptive throughout the study to maintain stable hormone levels. Females not on oral contraceptives will be measured at identical times in their menstrual cycle. As this is a cross-over model and subjects are their own control, potential differences in baseline FMD are not to be expected to influence results. For both trials, volunteers eligible for trial participation will receive study medication and instructions how to use it. The first study is a randomized, single-blinded cross-over study. 26 participants will be recruited and half of the participants will be pretreated with metformin 500 mg three times a day for 3 days, to ensure a steady state plasma concentration, whereas the other half will receive no medication. The two experiments will be separated by approximately two weeks to prevent any cross-over effect of metformin. The last dose of metformin will be given approximately 3 hours before the experiments. The FMD measurements will be performed, by an operator blinded for pretreatment after an overnight fast and 24 hours of caffeine abstinence (since caffeine is an adenosine receptor antagonist). Also, the participants have to refrain from strenuous exercise for at least 24 hours before the experiment, as this potentially act as a preconditioning stimulus. Experiments will be performed in a temperature-controlled room (22° C) and according to recent guidelines for assessment of the FMD. Measurements will always be performed at the same time of day to prevent diurnal variation in the FMD response.

When metformin displays a protective effect on endothelial function in this RCT, a second experiment will be conducted in the same volunteers to further elucidate the underlying mechanism. For this experiment the design will be identical to the metformin-FMD trial, with the exception that the subjects will all be pretreated with caffeine (4 mg/kg intravenously over 10 minutes) prior to the FMD measurement. This dose has previously been shown to completely prevent the protective effect of ischemic preconditioning which is also mediated by adenosine receptor stimulation in another human experimental model of forearm ischemia-reperfusion injury. This study will provide the answer to the question whether the protective effect of metformin is mediated by adenosine receptor stimulation by comparing the results of the FMD measurements with and without concomitant administration of caffeine. In addition, this study will enable us to exclude that any effect of caffeine on metformin-induced protection is due to a direct effect of caffeine on FMD or on the effect of IR on FMD: this will be studied by comparing the FMD measurements after caffeine administration in the placebo-arms.

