##### 4.4 Sample size calculation

A recent study with a similar experimental design from our research group has reported that the FMD averages 7.7% before, and 5.1% after forearm IR. Therefore, the effect of IR

on FMD is 2.6% with a SD of 3.7%. However, this study did not have a cross-over design. A previous cross-over study from [name] et al. (unpublished results) has reported a Spearman correlation coefficient of 0.53 between the two paired FMD measurements, but in this study one of the FMD measurements was preceded by ischemic preconditioning. Thus, the correlation coefficient with two similar measurements of FMD is most likely stronger than 0.53. Assuming a correlation coefficient of 0.7, the expected SD of the effect of IR on FMD in our study therefore equals 2.85. With  $n = 26$  subjects, we will be able to detect a difference of 1.65% with a power of 80% and a type I error probability of 5%, which is a relevant difference.

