### **9.2 Univariate analysis**

A paired-sample t-test will be used to test whether metformin can attenuate the decrease in FMD after forearm IR. The same method will be used in the second study to explore the effect of caffeine on metformin-induced protection, and the effect of caffeine on FMD per se.

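### Study 2 promises to exclude a direct effect of caffeine on FMD, but the only method fixed is a paired t-test for a difference, with no margin or interval criterion

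*Protocol*

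**What the plan says.** Section 3 (Study design) gives the second study two tasks. One is to show whether metformin's protection runs through adenosine receptors. The other is a safeguard: "this study will enable us to exclude that any effect of caffeine on metformin-induced protection is due to a direct effect of caffeine on FMD", and the same sentence extends this to the effect of IR on FMD. The comparison is named: "this will be studied by comparing the FMD measurements after caffeine administration in the placebo-arms". There is no placebo in this trial, so these arms must be the sessions without metformin.

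Section 9.2 fixes the method. For the first study, "A paired-sample t-test will be used to test whether metformin can attenuate the decrease in FMD after forearm IR". For the second, "The same method will be used in the second study to explore the effect of caffeine on metformin-induced protection". The sentence then adds a further target for that test: "and the effect of caffeine on FMD per se".

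The only sample size calculation is in section 4.4. It is about detecting a difference in a sample of 26: "we will be able to detect a difference of 1.65% with a power of 80% and a type I error probability of 5"%. It calls that difference relevant. No margin, interval criterion or power is given for the caffeine comparison.

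**The concern.** Section 3 announces a conclusion of absence, and section 9.2 supplies a test that can only show presence. Without a margin or an interval rule, the one test outcome that could lead to the word *exclude* is a non-significant p-value, and that means only that nothing was detected. Such a rule also works backwards: the noisier the FMD data, the easier it is to call a direct effect excluded.

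At stake is the mechanistic claim. If caffeine itself lowers FMD or worsens IR injury, part of an apparent loss of metformin protection could come from caffeine and be credited to blocked adenosine receptors. The primary metformin comparison in the first study is not affected.

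**Working it through.** **Inputs (section 4.4 unless noted).** n = 26, paired, with section 3 using the same volunteers in both studies; SD 3.7 from a study that was not a cross-over; correlation 0.7 assumed and 0.53 observed; SD 2.85 used; relevant difference 1.65 points; IR effect on FMD 2.6 points; type I error 5%. Sidedness is not stated; two-sided reproduces the protocol's figure.

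**Reproducing the protocol's figure.**
- SD of a paired difference = 3.7 × √(2 × (1 − 0.7)) = 2.866, stated as 2.85.
- Standard error = 2.85/√26 = 0.559. Noncentrality for 1.65 = 1.65/0.559 = 2.95, with 25 degrees of freedom.
- Power from the noncentral t distribution = 81.0% (80.5% with SD 2.866). This agrees with the stated 80%.

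**Assumption for the caffeine comparison.** The 2.85 is given for the effect of IR on FMD. No SD is given for FMD with versus without caffeine, so 2.85 is borrowed. The upper end of the range uses the observed correlation: 3.7 × √(2 × (1 − 0.53)) = 3.59, standard error 3.59/√26 = 0.70.

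**Chance that the paired t-test misses a true direct caffeine effect.** Miss rate = 1 − power, two-sided 5%, 25 degrees of freedom.

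| True effect (FMD points) | SD 2.85 | SD 3.59 |
|---|---|---|
| 1.65, the protocol's relevant difference | 19% | 38% |
| 1.3 = 2.6/2, half the IR effect | 39% | 57% |
| 0.825 = 1.65/2, half the relevant difference | 71% | 80% |

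**What a non-significant result leaves open.** The half-width of the 95% confidence interval is 2.06 × 0.559 = 1.15 at SD 2.85, and 1.45 at SD 3.59. With a true effect of 0.825, the test is non-significant while the 95% interval still contains 1.65 in about 41% of trials (SD 2.85) or 59% to 60% (SD 3.59). In those trials the data themselves would not rule out the relevant difference.

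**An interval rule instead.** Declare exclusion only if the 90% confidence interval lies inside ±margin, which is the same as two one-sided 5% tests. With a margin of 1.65 and n = 26, the chance of declaring exclusion is:

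| True direct effect | SD 2.85 | SD 3.59 |
|---|---|---|
| 0 | 78% | 48% |
| 0.825 | 41% | 27% |
| 1.65 | 5% | 5% |

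If p > 0.05 were read as exclusion, the corresponding figures would be 95%, 71% and 19% at SD 2.85, and 95%, 80% and 38% at SD 3.59.

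Narrower margins cost more. With no true effect, a margin of 1.3 succeeds in 46% (SD 2.85) or 15% (SD 3.59), and a margin of 0.825 in 2% or under 1%.

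**The case against.** **The decision rule is inferred.** A reader might conclude that the protocol declares p > 0.05 to be proof of no effect. It does not say so. Section 9.2 uses the softer verb *explore*, a paired t-test also yields a mean difference and an interval, and interpretation rules are often left to a SAP, which is not at hand. This stands as a limit on the point. It does not remove it: the protocol states both the claim and the method, and as written they do not fit.

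**The mechanistic conclusion need not hinge on this exclusion.** A reader might infer that attribution to adenosine receptors fails without it. In study 2 caffeine is given in both the metformin and the no-metformin session. If protection (metformin minus no metformin) is compared with and without caffeine, an additive direct effect of caffeine cancels. Sections 2 and 9.2 can be read that way. The harm is greatest if attenuation is judged from the metformin sessions alone, and the protocol does not settle which contrast is meant. This objection largely stands against the size of the harm, but not against the unsupported promise in section 3.

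**The benchmark for a relevant effect.** A reader might quote higher miss rates for relevant effects, for example 31% for an effect of half an SD (0.5 × 2.85 = 1.425 points) or 71% for 0.825 points. The protocol calls only 1.65 points relevant, for which the rate is 19% (38%). The smaller effects show how the test behaves; they are not thresholds the protocol sets.

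**A margin of 1.65 is generous.** It equals the whole target difference, so an effect half that size would still be declared excluded in 41% (27%) of trials. This stands, and the fix takes it into account.

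**Conclusion.** The point holds as a mismatch between claim and method. Section 3 promises to exclude a direct caffeine effect on two quantities, FMD itself and the IR effect on FMD, and the only method fixed is a difference test that cannot deliver that conclusion. For the one difference the protocol calls relevant, the test would miss a true effect in about one trial in five, or nearly two in five if the correlation is 0.53.

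These rates assume 26 complete pairs, a two-sided 5% test, normally distributed differences, and the section 4.4 SD carried over to the caffeine comparison. The mismatch depends on none of them. It should be corrected because it changes what study 2 may conclude, but the documents do not support saying that the adenosine conclusion fails without it.

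**What to change.** - **Section 9.2:** for the sessions without metformin, report the paired difference (caffeine minus no caffeine), once for FMD before IR and once for the IR-induced change in FMD, each with a confidence interval.
- **Section 3:** replace the promise to exclude a direct effect with a statement that the study will estimate it. Claim exclusion only of effects beyond a stated margin, and only if the 90% confidence interval lies inside that margin. Otherwise report the interval and state that a direct effect could not be excluded.
- **Margin:** fix it before study 2 data are seen, no wider than 1.65 points and preferably narrower.

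The change is to wording only: same data, subjects and visits. The cost is that exclusion becomes harder to claim. With no true effect and a margin of 1.65, it succeeds in about 78% (48%) of trials for each quantity. Requiring both lowers this; if the two were independent, which is an assumption, to about 0.78² = 61% (0.48² = 23%). A narrower margin lowers it further: at 1.3 points and SD 2.85, about 43 subjects would be needed for 80% success per quantity. If the sponsor will not accept that, the statement should be limited to estimation.
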